##### Social participation

An adapted version of the Dutch questionnaire Visuele Activiteiten en Participatie (VAP; Visual Activities and Participation) will be used to measure social participation [30]. Using a 10-point scale, this questionnaire measures the ability to perform a certain task of daily living and the participant’s perception about whether this performance is normal or problematic. The original questionnaire for adolescents consists of ten domains, each containing four questions. Answering these questions allows three subdomains to be distinguished: visual competence (Cronbach’s alpha .94), self-reliance (.83), and participation perception (.91) [30]. In this study five of the ten domains will be used, each with four questions, using two subdomains (self-reliance and participation perception).

##### Work/education

To measure type of education, history of education (special or regular schools), and level of education, three closed-ended questions will be used. For employment, 11 questions measuring type of job, voluntary or unpaid employment hours, travel hours, side jobs, and the maximum working hours per week are asked.

##### Leisure activities

To assess the leisure activities of the adolescents, a Dutch translation of the Degree of Peer Activity (DPAL) questionnaire will be used to measure the amount and frequency of peer contact [31, 32]. This questionnaire consists of five items with a six-point scale with answers ranging from “never” to “every day”. The internal consistency was found to be .66 [31]. All participants will furthermore be asked about their activities during leisure time with 20 questions about sports, hobbies, affiliation with political or religious groups, hours spent on activities during leisure time, and reasons for participating in these activities. Using the Internet, including social media, is one of the most common leisure activities performed by adolescents today [33, 34]. Therefore, this study will include four questions to measure type and frequency of Internet and social media use. Also a Dutch version of The Multidimensional Scale of Facebook Use (MSFU), with ten items and a six-point scale, will be adapted and used to measure social media use [35]. The original scale measured three dimensions of Facebook use: passive Facebook use (Cronbach’s alpha .52), active private Facebook use (.66), and active public Facebook use (.84) [35]. In this study the questionnaire is adapted to general social media use, and a seventh answer on the scale, namely “multiple times per hour”, is added. To measure the perceived online social support on social media, a questionnaire with four items and a five-point scale will be used. These questions are based on the family subscale of the Multidimensional Scale of Perceived Social Support [36]. The internal consistency of this scale was found to be .95 [37].

##### Social relationships

The Social Network Map [5, 6, 38–40] will be used to measure the size and composition of the social network of the adolescents. With this scale each sector or category such as family, extended family (for example, uncle, aunt, niece), friends, and professionals/therapists can be outlined. It measures the amount of people in each sector and the importance of these relationships. Social support will be measured by the personal network list (PNL) with the role-relation method [3, 41]. This seven-item questionnaire measures the social support during leisure activities, problems at school/work, and social relationship problems with answers ranging from 10 “not important” to 100 “really important”. The internal consistency was found to be .76, .79, and .81 [41]. Satisfaction with the social network is measured with two items: “*How satisfied are you with the support you get with practical problems?”* and *“How satisfied are you with the support you get for personal problems?”.* Answers are given on a five-point scale. Developing and maintaining romantic relationships is a common interest during adolescence [14, 42, 43]. To assess this topic, 12 questions will be used, for example, “*Do you have a romantic partner*?”, “*How long has this relationship lasted*?”, and “*Have you ever fallen in love?*”.

#### Measures of mediating variables

##### Well-being

General well-being will be measured with a Dutch translation of the well-being measure developed by Cantrill [44], which asks “*How do you feel in general?*”. The response is given on a ten-point scale, by choosing a number between 1 (feel really bad) and 10 (feel really good). Three items are added regarding well-being in the domains of leisure activities/sport, network of friends, and school/work [3, 5].

##### Self-perception social competence

Perceived social competence will be measured with a Dutch version of Harter’s Self-Perception Profile [45]. In this study four domains (physical appearance, sociability, intimate relationships, and social acceptance) of the questionnaire will be used with each of four items. Each item consists of two opposing statements. Participants have to choose the description that fits them best and then indicate whether this description is true or very true for them. The internal consistencies of these subscales were found to be: .77, .69, .56, and .62 [45].

##### Self-esteem

To measure self-esteem, the Dutch version of the Rosenberg Self-Esteem Scale (RSES) [46] will be administered. This scale comprises 10 items (for example, “*I take a positive attitude towards myself*”). Answers are scored on a four-point Likert scale, with an internal consistency of .85 [47].

##### Loneliness

To assess loneliness, the questionnaire of De Jong-Gierveld will be used [48]. This questionnaire consists of 11 items with answer categories: “yes”, “no”, and “more or less”. With the answers to this questionnaire, two subscales of loneliness can be computed: emotional loneliness and social loneliness with an internal consistency of .81 and .68 [6].

##### Acceptance of the impairment

Acceptance of the impairment will be measured using a subscale of the Nottingham Adjustment Scale (NAS) [49, 50]. This subscale contains nine items. An example of an item is: “*I feel bad when I realize what sighted people can do and what I can’t*”. Answers will be scored on a five-point Likert scale. One positively formulated item is added: “*My visual impairment is part of me, but doesn’t determine what I do or think*”. Internal consistency was found to be .81 [5].

##### Coping

Coping will be measured by the Cognitive Emotion Regulation Questionnaire (CERQ) [51]. This scale consists of 36 items and answers will be scored on a four-point Likert scale. With the answers to these questions, nine subdomains of cognitive coping can be distinguished. The internal consistency of the subdomains ranges from .68 to .83 [51–53].

##### Self-determination

Self-determination will be measured with the Basic Psychological Need Satisfaction and Need Frustration (BPNSF) scale [54]. This 24-item questionnaire with a five-point Likert scale measures the basic psychological needs and need frustration for autonomy, relatedness, and competence. The internal consistency ranges between .64 and .89 [54].

#### Predictor variables

Predictors that might distinguish adolescents who benefit from the interventions include demographic factors and personality.

##### Personality

To measure personality, a Dutch version of the Big Five questionnaire with 30 items and a seven-point answer scale is used [55]. From this scale five different domains or dimensions of personality can be distinguished: extraversion, neuroticism, openness to experience, agreeableness, and conscientiousness. The internal consistency ranges from .68 to .90 [56].

##### Demographic characteristics

15 open-ended and closed questions will be used to collect participants’ demographic information concerning gender, age, nationality, ethnic origin, living situation, and characteristics of their home and family.

#### Control variables

Degree of visual impairment, mobility, and treatment integrity will be measured and used as control variables.

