### Hypotheses

The main hypothesis in this study is:Adolescents who are assigned to Mentor Support will improve their social participation more strongly in comparison with adolescents assigned to care-as-usual only.

The secondary hypotheses in this study are:Adolescents who are assigned to Mentor Support receiving the intervention from a mentor with a visual impairment will improve their social participation as much as adolescents receiving the intervention from a mentor who is sighted.Adolescents who are assigned to Mentor Support will improve their psychosocial functioning and feeling of self-determination.Adolescents who are assigned to Mentor Support and are self-determined or have a high level of psychosocial functioning will improve their social participation more strongly.

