Meeting 6	Hobbies and searching for possibilities	Leisure activities
Meeting 7	Preparing a party and inviting new friends	Social relationships
Meeting 8	Presentation skills and appearance	School/work
Meeting 9	Out of the box or out of your comfort zone	Leisure activities
Meeting 10	Searching for your motto in life and role model(s)	School/work
Meeting 11	Discussing romantic relationships, flirting and dating	Social relationships
Meeting 12	Evaluating the intervention during special leisure activity	Leisure activities

Participants randomized to the control group will receive only care-as-usual. The two national organizations for people with VI in the Netherlands offer a wide range of services, such as mobility training, and itinerant teacher support at school. At pre-test, post-test, and follow-up all participants are asked about the kind and amount of care-as-usual service they have received.

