##### Treatment integrity

To assess whether the intervention is carried out according to the Mentor Support manual, all dyads have to fill out an evaluation form after every meeting. These forms will show what kind of activity, how long, and which assignments or exercises they have performed.

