### Data analyses

Most analyses will be conducted using the software program Statistical Package for the Social Sciences (SPSS). The descriptive analyses will be carried out using standard methods. If necessary, outliers will be checked and winsorized before analyzing. Differences in baseline characteristics between both experimental groups and the care-as-usual-only group will be analyzed and results will be controlled for these differences if needed. For analyzing the primary (social participation on three domains), mediation (psychosocial functioning and self-determination), and predictor (demographic factors and personality) outcomes, ANOVA repeated measures or multilevel analyses will be used. The primary outcomes of participants in both experimental groups will be compared separately from the care-as-usual-only group. Pre-test, post-test, and follow-up will show the change in quantity and quality of social participation, psychosocial functioning, and self-determination as compared with the care-as-usual-only group, over time. Feasibility of the Mentor Support intervention will be analyzed using descriptive analyses. General mixture modeling with M-plus [58] will be used to examine the impact of the Mentor Support intervention on subgroups. Analyses and reporting of the results will be done according to the CONSORT Statement guidelines.

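### Treatment integrity is listed as a control variable, although it arises after randomisation and has no value in the care-as-usual arm; it should be kept out of between-arm comparisons

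*Protocol article*

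**What the plan says.** The Control variables section gives three variables the same role: "Degree of visual impairment, mobility, and treatment integrity will be measured and used as control variables". The first two describe the participant. The third is defined under Treatment integrity, where "all dyads have to fill out an evaluation form after every meeting" and "These forms will show what kind of activity, how long, and which assignments or exercises they have performed".

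The control arm has no dyads. Under Intervention, "Participants randomized to the control group will receive only care-as-usual".

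The main hypothesis is a comparison by assignment: "Adolescents who are assigned to Mentor Support will improve their social participation more strongly in comparison with adolescents assigned to care-as-usual only". Under Data analyses, "The primary outcomes of participants in both experimental groups will be compared separately from the care-as-usual-only group", and "ANOVA repeated measures or multilevel analyses will be used". The only adjustment rule in that section concerns imbalance in baseline characteristics: "results will be controlled for these differences if needed". It does not mention the control variables or treatment integrity. The Abstract and the Selective attrition section commit to intention-to-treat analysis.

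**The concern.** A covariate in a randomised comparison should be fixed before allocation. Treatment integrity records how the programme was delivered, so it is produced by the arm the participant was allocated to. It has no natural value for a participant without a mentor.

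If it enters a model comparing a mentored arm with care-as-usual, the arm coefficient may no longer be the effect of being assigned to Mentor Support, which is what the main hypothesis and the intention-to-treat commitment call for. The planned power would not carry over to that model either.

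The secondary comparison of mentors with and without visual impairment is also exposed. Integrity is defined in both of those arms, but the type of mentor may influence how meetings run. Adjusting for integrity would then condition on a possible consequence of the factor being compared.

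**Working it through.** **1. The plan's own power figure.** For the between-subject test in repeated-measures ANOVA, λ = f²·N·m / (1 + (m − 1)ρ), with f = d/2 = .25, 3 groups and m = 3 assessments. The article gives no ρ; I assume .5.
- N = 120: λ = .0625 × 120 × 3 / 2 = 11.25, power .851 (stated: .85).
- N = 108: λ = .0625 × 108 × 3 / 2 = 10.125, power .809 (stated: .80).

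The stated figures reproduce, for a model without an integrity covariate.

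**2. What the covariate does, by coding of the controls.** Take one standardised outcome (residual SD 1) regressed on arm and integrity, with n_t mentored and n_c control participants. Let M and S be the mean and SD of integrity among the mentored.

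*Controls coded 0.* Controls carry no information on the integrity slope b, so the slope is estimated in the mentored arms alone. The arm coefficient is

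(mean of mentored − mean of controls) − b·M,

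which is the predicted difference at zero meetings. Its standard error is

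√[1/n_t + 1/n_c + M² / ((n_t − 1)S²)].

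Without the covariate the last term vanishes.

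*Controls coded missing.* A complete-case analysis drops every control, and the contrast cannot be estimated.

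*Integrity centred within the mentored arms, controls 0.* Then M = 0. The arm coefficient is the unadjusted mean difference, with essentially the same standard error.

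**3. Numbers for coding controls as 0.** From the article: 40 per arm, so 80 v 40 when the mentored arms are pooled; d = .5; α = .05; 12 meetings. Assumed, because the article gives no integrity score or distribution: integrity is the number of meetings held, and the test is two-sided.
- No covariate: √(1/80 + 1/40) = √.0375 = .19; power .73.
- M = 10, S = 2: √(.0375 + 100/(79 × 4)) = √(.0375 + .3165) = .595.
- M = 7, S = 3.5: √(.0375 + 49/(79 × 12.25)) = √(.0375 + .0506) = .297.

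Meetings cannot exceed 12. Capping reduces S, so the simulated standard errors (4,000 runs, true effect .5 SD) are somewhat larger than these.

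| Assumed meetings, capped at 12 | SE of arm effect | Power, benefit unrelated to meetings |
|---|---|---|
| No covariate | .19 | about .72 |
| Mean 10, SD 2 | .66 | .11 to .12 |
| Mean 8, SD 3 | .37 | .26 |
| Mean 7, SD 3.5 | .31 | about .35 |

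If benefit is instead proportional to meetings, the adjusted arm estimate is about 0 in each covariate row and is declared significant about 5% of the time, against about 70% without the covariate. With centred coding and mean 10, SD 2, the estimate is about .5, the SE .19 and power .71 to .74, as with no covariate.

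**4. Each mentored arm separately against control (40 v 40).** With integrity scored as the share of sessions delivered, controls at 0 and benefit unrelated to integrity: at mean .8, SD .2, the SE rises from .22 to .77 and power falls from .58 to .09; at mean .6, SD .3, the SE rises to .42 and power falls from .61 to .21.

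**5. Shared causes.** If a prognostic factor drives both integrity and outcome (assumed loading .5 on each; mean share .8, SD .2; 80 v 40; controls at 0), the adjusted arm coefficient becomes −.60 when benefit is unrelated to sessions and −1.09 when it runs through them, although the true effect is +.5.

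**The case against.** The strongest reply is that the article never says integrity enters the comparison with care-as-usual. The control-variables sentence stands in the Measures section. The Data analyses section adjusts only for baseline differences, and integrity is not a baseline quantity. The stated purpose of the forms is to check that the manual was followed, and the article also plans a descriptive feasibility analysis. A condensed article may leave the assignment of covariates to models to the analysis plan.

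This stands as a limit on certainty. A reader might infer that the primary test will be adjusted for integrity, and that a working programme would then be reported as ineffective. The documents do not establish either step. The harm arises only if integrity enters a between-arm model, and only under some codings. If controls were coded missing, the analysis would fail visibly rather than give a misleading null result.

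A reader might also infer that any use of integrity as a covariate destroys the arm effect. It does not: centring within the mentored arms leaves the comparison with care-as-usual intact.

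The reply does not remove the point. The article makes a positive commitment to use integrity as a control variable, places it beside two participant characteristics, and nowhere confines it to the mentored arms, to description or to exploration. Even confined to the mentored arms, it would remain a post-randomisation covariate in the comparison of mentor types.

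**Conclusion.** The point holds in conditional form. The article wrongly gives the role of control variable to a quantity that arises after randomisation and does not exist in the control arm. Which model it enters is left open.

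On the plain reading, and with controls coded 0, the standard error of the arm effect grows by a factor of about 1.6 to 3.5 (.31/.19 to .66/.19), power falls from about .72 to between .11 and .36, and the arm effect is about 0 if benefit is proportional to meetings. These sizes rest on assumed means of 7 to 10 and SDs of 2 to 3.5 of 12 meetings, a single outcome, 80 v 40 and a true effect of .5 SD. They illustrate the problem and do not forecast this trial. That the coefficient under this coding refers to zero meetings does not depend on those assumptions.

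**What to change.** Remove treatment integrity from the control variables for all between-arm comparisons, both against care-as-usual and between mentor types. Keep only degree of visual impairment and mobility, and state that both are taken as measured at T1. Report integrity descriptively by mentored arm. If a dose question is of interest, put it in a labelled exploratory analysis within the mentored arms, outside the test of the main hypothesis.

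The cost is one sentence in the control-variables section and the matching line in the analysis plan. The evaluation forms are still collected, and no data or sample size change is needed.

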##### Degree of visual impairment

The Functional Vision Scale of Weiner [57] will be used to measure functional vision. This six-item questionnaire with answer categories “yes” and “no” categorized participants in three groups: moderate low vision, severe low vision, and blind. Participants will be categorized as blind if they use Braille, as having severe low vision if they cannot read regular print but do not use Braille, and as having moderate low vision if they can read regular print. Further, questions will be asked about the onset and course of the impairment as well as the medical diagnosis. Seven closed-ended questions will be used to measure additional impairments or chronic diseases and one closed question will measure their perceived level of general health.

##### Mobility

Two questions on level of mobility, independence in traveling and use of aids will be used to measure mobility [5].

##### Treatment integrity

To assess whether the intervention is carried out according to the Mentor Support manual, all dyads have to fill out an evaluation form after every meeting. These forms will show what kind of activity, how long, and which assignments or exercises they have performed.

### Sample size

The total sample size is based on the expected differences in outcome measures between participants assigned to the experimental arm receiving Mentor Support and the care-as-usual-only arm. For testing the significance of the between-subject factor (primary hypothesis) a sample of 120 participants (40 in each condition) is necessary to achieve an adequate power of .85 within a medium effect size (d = .5) between the conditions over time with a significance level of .05. Due to dropout or unexpected organizational aspects the number of participants could drop to as low as 108 to achieve a high power of .80. To answer the research question concerning the influence of potential mediators or predictors on the effectiveness of Mentor Support, several repeated measures within-between interaction analyses will be performed. Based on a significant level of .05 and a power of .85 (*f* = .25), a total sample size of 110 is needed.

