### Randomization

Upon signing the informed consent, before randomization, participants agree to be allocated to one of the three groups. An independent researcher will randomly assign participants at an individual level to one of the three arms of this randomized controlled study. The allocation will take place with a computerized random number generator after the baseline measurement and before the start of the intervention. Randomization stratification on the important factor of geographic proximity will be used to make sure there is equal allocation to regions. Blocking randomization in each region with a block size of 15 participants will be used to strive for regional groups with the same size. The independent researcher will keep the results of the randomization until the study is completed and all eligible participants are allocated. During the study the primary researcher and participants are not blinded. Only the researchers measuring the post-test and follow-up will be unaware of who is allocated to which arm.

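### The stated power of .85 at 120 and .80 at 108 belongs to a three-group main effect that averages in the pre-test, not to a test of greater improvement

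*Protocol article*

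**What the plan says.** The main hypothesis is that adolescents given Mentor Support "will improve their social participation more strongly in comparison with adolescents assigned to care-as-usual only". There are three assessments: pre-test (T1), post-test at 12 months (T2) and follow-up at 18 months (T3). Under Randomization: "The allocation will take place with a computerized random number generator after the baseline measurement". T1 therefore precedes allocation.

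The Sample size section reads "For testing the significance of the between-subject factor (primary hypothesis) a sample of 120 participants (40 in each condition) is necessary", and gives the operating characteristics as "adequate power of .85 within a medium effect size (d = .5) between the conditions over time with a significance level of .05". It then allows for losses: "the number of participants could drop to as low as 108 to achieve a high power of .80". For mediators and predictors it turns to a different test, "several repeated measures within-between interaction analyses will be performed", with its own calculation: "Based on a significant level of .05 and a power of .85 (*f* = .25), a total sample size of 110 is needed". No correlation between assessments is given for either calculation.

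The Data analyses section plans repeated-measures ANOVA or multilevel models over the three assessments. It compares each experimental group with care-as-usual, describes the result as change over time, and controls for baseline differences only if needed.

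**The concern.** The between-subject factor in a repeated-measures ANOVA compares the groups on their average over all occasions. With a pre-randomisation assessment among those occasions, the expected group difference at T1 is zero, so the average understates any treatment effect. A hypothesis about improvement is answered by a group-by-time or baseline-adjusted comparison. If the published power was computed for the main effect, it does not describe the power for the main hypothesis, and the floor of 108 is not justified by it. A null result could then be read as coming from a trial with .80 to .85 power when the test actually run had less.

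**Working it through.** **Inputs.** From the article: 3 groups, 3 occasions, N = 120 or 108 in equal arms, alpha .05 (taken as two-sided for t tests), d = .5, and f = .25 (stated for the second calculation in the same section). Assumed: equal variances and a common correlation r between occasions, .5 unless stated, with a range of .3 to .7.

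**1. Reproducing the stated figures.** For the between-subject main effect with m = 3 occasions, the noncentrality is λ = N f² m / (1 + (m − 1) r), on 2 and N − 3 df.
- N = 120: λ = 120 × .0625 × 3 / 2 = 11.25, power .851.
- N = 108: λ = 10.125, power .809.
- One participant fewer per arm misses each target: N = 117 gives .842 and N = 105 gives .797.

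So 120 and 108 are the smallest equal-arm totals reaching .85 and .80, for the test that the section names.

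**2. d is not f here.** With group means (0, .5, .5) the overall mean is 1/3 and f² = (1/9 + 1/36 + 1/36)/3 = 1/18, so f = .236. The value f = .25 corresponds to d = .5 only for two equal groups. Even if the full difference were present at all three occasions:
- N = 120: λ = 120 × (1/18) × 3 / 2 = 10.0, power about .80.
- N = 108: λ = 9.0, power .76.

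**3. Dilution by T1.** With a difference of 0 at T1 and .5 at T2 and T3, the averaged difference is (0 + .5 + .5)/3 = .333, so λ is multiplied by (2/3)² = 4/9.
- N = 120: λ = 4.44, power .45 (.54 at r = .3; .38 at r = .7).
- N = 108: λ = 4.0, power .41 (.49 at r = .3; .34 at r = .7).

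**4. Tests of improvement suggested by the Data analyses section**, with d = .5 at T2 and T3.
- Three-group group-by-time (4 df): the interaction effects have sum of squares .25 × (2/3) × (2/3) = 1/9, so λ = 40 × (1/9) / (1 − r). At r = .5, λ = 8.89 and power is .65 at 120 (.59 at 108). At 120 it is .49 for r = .3 and .88 for r = .7.
- One arm v control, group-by-time (2 df): λ = .25 × (40/2) × (2/3) / (1 − r) = 6.67 at r = .5, power .62.
- One arm v control, T1-to-T2 change: the SD of change is √(2(1 − r)) = 1 at r = .5, so this is a 40 v 40 t test at d = .5, power .60.

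**5. Baseline-adjusted contrasts.** Adjusting for T1 leaves residual variance 1 − r² for T2 alone (.75 at r = .5), and (1 + r)/2 − r² for the mean of T2 and T3 (.50 at r = .5). Two-sided t tests give:

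| Contrast, adjusted for T1 | r = .5: N = 120 | r = .5: N = 108 | r = .3: N = 120 | r = .3: N = 108 |
|---|---|---|---|---|
| Pooled v control, T2 | .84 | .80 | .77 | .72 |
| Pooled v control, mean of T2 and T3 | .95 | .93 | .93 | .90 |
| One arm v control, T2 | .72 | .68 | .64 | .59 |
| One arm v control, mean of T2 and T3 | .88 | .84 | .84 | .80 |

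**The case against.** A reader might infer that the trial is underpowered for its main hypothesis. The documents do not support that. The main hypothesis sets Mentor Support as a whole against care-as-usual, and mentor type is secondary, so a pooled 80 v 40 comparison is a fair reading. Adjusted for T1, it gives .84 and .80 at r = .5, within .01 of the published figures. The mean of T2 and T3, adjusted for T1, does better still, even for a single arm at 40 v 40 (.88). A multilevel model could deliver that comparison. This part of the objection stands.

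The origin of the figures is also inferred. The section states neither a correlation nor the number of occasions used, and a pooled adjusted contrast fits nearly as well. But the section names the between-subject factor, no pooled adjusted contrast is described anywhere, and baseline adjustment is conditional.

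The phrase "within a medium effect size (d = .5) between the conditions over time with a significance level of .05" could be taken to mean an interaction. The numbers do not fit: a three-group interaction at f = .25 and r = .5 has power above .99, and the section keeps interaction tests for mediators and predictors. (The d = .5 pattern above corresponds to an interaction f of only about .11, so that high figure does not carry over.)

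A higher correlation helps the group-by-time test, which reaches .88 at r = .7. The main effect at f = .25 then falls to .78 at 120, so that value would not support the published figure for the test it names.

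Nor does the point ask for detail that an article may leave to an analysis plan. It concerns a test, an effect size and a power that the article does state.

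**Conclusion.** The stated power is attached to the wrong test. As a main effect with d = .5 arising only after treatment, it would be about .45 at 120 and .41 at 108, not .85 and .80. The d-to-f mismatch alone lowers the figures to about .80 and .76. At correlation .5 the repeated-measures tests of improvement have about .60 to .65 at 120. The size of that shortfall depends on an unstated correlation (.49 to .88 for the three-group test over .3 to .7) and on a model that the article leaves open between repeated-measures ANOVA and multilevel analysis. What is firm is that the named test does not answer the hypothesis. Whether 120 or 108 participants suffice depends on which contrast is fixed as primary, and with a baseline-adjusted pooled contrast they can.

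**What to change.** - In the Sample size section, remove the reference to the between-subject factor.
- In both the Sample size and Data analyses sections, name one baseline-adjusted pooled contrast, Mentor Support (80) v care-as-usual (40), as the primary test. Say whether it uses T2 alone or the mean of T2 and T3.
- State the assumed correlation and the power that goes with it. At .5 these are .84 at 120 and .80 at 108 for T2, or .95 and .93 for the mean of T2 and T3. Give a lower correlation as well: at .3 the T2 contrast has .77 and .72.
- State the lower power of each single arm v control under the same model (at correlation .5 and 40 v 40: .72 for T2 adjusted, .88 for the adjusted mean of T2 and T3), and .60 for the unadjusted comparison.

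The cost is more than rewording the sample-size paragraph. No such contrast is planned at present, so the analysis text changes too, and this should be settled before outcomes are compared by arm. No extra participants are needed. Some of the stated powers become less favourable.
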